| Individual treatment                                       |                      |                                  | √                    | √                                | √                                                                 | √                                                                             | √                                                                      | (√)                                                                                 |                                                         |
| ADLA questionnaire                                         |                      | √                                | √                    | √                                | √                                                                 | √                                                                             | √                                                                      | (√)                                                                                 | √                                                       |
| AEs                                                        |                      |                                  |                      | √                                | √                                                                 | √                                                                             | √                                                                      | (√)                                                                                 | √                                                       |
| End of study record                                        |                      |                                  |                      |                                  |                                                                   |                                                                               |                                                                        |                                                                                     |                                                         |

a Visit 2 (Baseline) should take place max. 28 days after visit 1 (Screening). If that is not the case, blood tests have to be repeated.

b Visit 3 (Treatment) should start on the same day or one day after visit 2

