(Baseline). If that is not the case, the pregnancy test has to be repeated and in case the period between the two visits is > 28 days also blood tests and check of in- and exclusion criteria have to be repeated.

c only to be done if not already done on day 22

d only to be done if not already done on day 42

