## **8.2 Laboratory Evaluation**

### **8.2.1 Blood**

Blood samples with volumes between 5 – 25 ml will be taken during screening (24 ml), before treatment no. 22 (4.9 ml) and after treatment no. 42 (10.4 ml) as well as 6, 12 and 24 months after treatment onset (19.9 ml, respectively) to do the assessments described below as well as in chapter 8.3.

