#### **8.2.1.1 Hematology and biochemistry**

At baseline venipuncture will be performed for assessing the full bloodcell count, transaminases, creatinine and bilirubin. Transaminases will also be checked before treatment no. 22 and on the last day of treatment (after treatment no. 42).

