## 8.3 Schedule of Events

The study consists of the following visits (see also chapter 3 “Schedule of activities”):

|           |                                                                                                                                        |
|-----------|----------------------------------------------------------------------------------------------------------------------------------------|
| Visit 1:  | Screening Visit                                                                                                                        |
| Visit 2:  | Enrolment Visit (max. 28 days after screening)                                                                                         |
| Visit 3:  | Treatment
Treatment start (Day 1) - Daily observed treatment with 42 doses of Doxycycline -
Treatment end (Day 43 + max. 7 days) |
| Visit 4:  | 2 months follow-up (Day 61 ± 7 days)                                                                                                   |
| Visit 5:  | 4 months follow-up (4 month, Day 121 ± 10 days)                                                                                        |
| Visit 6:  | 6 months follow-up (6 month, Day 182 ± 21 days)                                                                                        |
| Visit 7:  | 8 months follow-up (8 month, Day 243 ± 14 days)                                                                                        |
| Visit 8:  | 10 months follow-up (10 month, Day 303 ± 14 days)                                                                                      |
| Visit 9:  | 12 months follow-up (12 month, Day 364 ± 21 days)                                                                                      |
| Visit 10: | 14 months follow-up (14 month, Day 425 ± 21 days)                                                                                      |
| Visit 11: | 16 months follow-up (16 month, Day 485 ± 21 days)                                                                                      |

|           |                                                      |
|-----------|------------------------------------------------------|
| Visit 12: | 18 months follow-up (18 month, Day 546 ± 21 days)    |
| Visit 13: | 20 months follow-up (20 month, Day 607 ± 21 days)    |
| Visit 14: | 22 months follow-up (22 month, Day 667 ± 21 days)    |
| Visit 15: | 24 months follow-up (24 month, Day 728 -28/+48 days) |

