### 8.3.1 Screening (Visit 1)

Members of the research team will identify potential subjects. The following assessments/ procedures will be performed during screening:

- Informed consent for screening procedures
- Demographic data
- Lymphedema staging
- History of lymphedema
- History of acute dermatolymphangioadenitis (ADLA)
- Medical history
- Concomitant medication
- History of trial relevant medication
- Physical examination
- Vital signs
- Laboratory assessment (24 ml of blood): Full blood cell count, Liver Function Tests (AST/ALT/γ-GT), Serum Creatinine, FTS, Microfilariae count (Sedgewick, in FTS positive participants only), biomarkers, T-cell activation markers
- Urine sampling (max. 25 ml)
- Urine pregnancy test (for women of childbearing potential). In addition, women of childbearing potential will be counseled on avoiding pregnancy during the treatment period in a culturally appropriate manner as defined by the local IRB.
- Saliva sampling (2 ml)
- Assessment of Inclusion/Exclusion criteria

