### **8.3.3 Treatment (Visit 3, day 1 – day 43 + 7 days range)**

#### **8.3.3.1 Treatment day 1**

- Urine pregnancy test if not done during visit 2 on the same day or one day before
- Concomitant medication
- Participants will receive the first dose of either doxycycline or placebo under supervision of the trial clinicians at the study sites.

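### Two separate 28-day limits leave the age of the eligibility bloods at first dose uncapped: 29 days on schedule, up to 56 days without a repeat if dosing is delayed

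*Protocol*

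**What the plan says.** **Where the bloods come from.** Section 8.2.1 states that samples "will be taken during screening (24 ml), before treatment no. 22 (4.9 ml) and after treatment no. 42 (10.4 ml"). Section 8.3.1 places the eligibility panel at screening: "Laboratory assessment (24 ml of blood): Full blood cell count, Liver Function Tests", together with creatinine. Section 8.2.1.1 speaks of baseline. However, the Section 3 table marks blood at Visit 2 and on day 1 as conditional only, under footnotes a and b, and the Visit 2 list in 8.3.2 contains no blood draw.

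**The two limits.** Footnote a reads "Visit 2 (Baseline) should take place max. 28 days after visit 1 (Screening"), with bloods repeated otherwise. Footnote b reads "Visit 3 (Treatment) should start on the same day or one day after visit 2" (Baseline). If that is missed, the pregnancy test is repeated, and where the "period between the two visits is > 28 days also blood tests and check of in- and exclusion criteria have to be repeated".

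**Elsewhere.** Section 8.3 restates only the first limit: "Enrolment Visit (max. 28 days after screening"). The day 1 list in 8.3.3.1 carries over only the pregnancy part of footnote b: "Urine pregnancy test if not done during visit 2 on the same day or one day before". Section 9.3 puts the investigations before the first dose but gives no time limit.

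**The concern.** Both footnotes treat 28 days as the point at which bloods need renewing. Each counts a visit interval, though, and not the age of the sample. The intervals add up, so a participant can be dosed on results twice as old as either limit suggests.

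What is at stake is the laboratory exclusion list in 7.8.3: haemoglobin, neutrophils, platelets, creatinine, AST, ALT and γ-GT. These values screen people before 42 doses of a drug for which 9.5.1 lists hepatotoxicity, a rise in BUN, neutropenia and thrombocytopenia, all without a reported frequency. After a delay of 2 to 28 days between Visits 2 and 3, neither the bloods nor the in-/exclusion check has to be repeated. For liver enzymes the next look comes during treatment: "Transaminases will also be checked before treatment no. 22 and on the last day of treatment (after treatment no. 42"). The visit lists in 8.3.3 to 8.3.9 contain no later creatinine or blood count.

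**Working it through.** The Protocol gives no figure for blood draw to first dose, so there is none to reproduce. Its stated figure is 28 days for each interval.

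**Inputs**
- x = days from Visit 1 to Visit 2. Bloods are repeated if x > 28 (footnote a).
- y = days from Visit 2 to Visit 3 (first dose). Planned y is 0 or 1. Bloods are repeated if y > 28 (footnote b).
- The draw is at Visit 1 (8.2.1, 8.3.1). I assume a footnote a repeat is drawn at Visit 2 and a footnote b repeat on day 1, as the table's conditional ticks indicate.

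**Age of the bloods at first dose**
- x ≤ 28 and y ≤ 28: age = x + y, no repeat.
- x > 28 and y ≤ 28: redrawn at Visit 2, so age = y, at most 28.
- y > 28: redrawn before dosing.

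**Maximum age with no repeat**
- On schedule: 28 + 1 = 29 days.
- Visit 3 delayed: 28 + 28 = 56 days.

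Enumerating all combinations of x and y from 0 to 60 days gives the same 29 and 56.

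**When bloods older than 29 days escape a repeat.** This needs x + y ≥ 30 with y ≤ 28, that is 30 − x ≤ y ≤ 28.

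| Visit 2 on day x | Delay y with no repeat | Age at first dose |
|---|---|---|
| 28 | 2–28 | 30–56 |
| 14 | 16–28 | 30–42 |
| 7 | 23–28 | 30–35 |
| 0 or 1 | none | – |

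**Uneven trigger.** With x = 1 and y = 29 the sample is 1 + 29 = 30 days old and must be redrawn. With x = 28 and y = 28 it is 56 days old and need not be.

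**Proposed rule:** repeat if y > 28, or if draw to first dose exceeds 29 days.

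| x + y | Age (days) | Current rule | Proposed rule |
|---|---|---|---|
| 28 + 1 | 29 | no repeat | no repeat |
| 28 + 28 | 56 | no repeat | repeat (new) |
| 1 + 29 | 30 | repeat | repeat |
| 0 + 29 | 29 | repeat | repeat (y > 28) |
| Redrawn at Visit 2, then y = 29 | 29 | repeat | repeat (y > 28) |

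The maximum age without a repeat falls from 56 to 29 days, and no repeat now required is lost.

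**The case against.** The strongest reply is that the Protocol contradicts nothing here. Inclusion criteria apply at randomization (7.8.2), which takes place at Visit 2, and footnote a does keep the bloods within 28 days at that point. Footnote b also governs the in-/exclusion check, last done at Visit 2, so counting from Visit 2 is natural for that part. The 56-day case needs a departure from the planned start with both intervals at their limit, and no passage sets a maximum sample age that is then missed.

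There are other safeguards too. Visit 2 repeats the physical examination, vital signs and eligibility check. Concomitant medication is reviewed on day 1, clinicians visit daily during treatment (10.9), and the investigator may withdraw someone whose baseline condition changes (13.2.2).

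Part of this stands. The case is off schedule and probably rare, and harm at 56 days is not shown. The safeguards are real, but they depend on a change being noticed, and none re-tests creatinine or blood count before the first dose.

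The argument from randomization does not settle the matter. Footnote b itself re-tests bloods before dosing, so the plan already treats their currency at first dose as relevant, yet it ignores their actual age. Delay is also foreseen: footnote b provides for a gap beyond 28 days, and 11.10.5 provides for drop-out between randomization and treatment start.

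**Conclusion.** The concern holds, at minor severity. The footnotes allow eligibility bloods up to 56 days old at first dose with only the pregnancy test repeated, against at most 29 days on the planned schedule. The rule also redraws a 30-day-old sample while letting a 56-day-old one pass.

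The conclusion rests on reading the two visits in footnote b as Visits 2 and 3, the only visits named there, and on the draw being at Visit 1. If the sponsor meant the period from blood draw to dose, the text does not say so and needs the same correction. The number of participants affected cannot be derived from the Protocol. With a planned gap of 0 or 1 day it is probably small. The point concerns safety screening only.

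**What to change.** Keep footnote b's existing trigger. Add that the blood tests and the in-/exclusion check are also repeated, with results seen before dosing, whenever the first dose falls more than 29 days after the most recent eligibility blood draw. Add a matching line to 8.3.3.1, which at present mentions only the pregnancy test. The limit is 29 days because 28 + 1 is the longest interval on the planned schedule. A 28-day limit would catch a participant who has Visit 2 on day 28 and is dosed the next day, exactly as planned.

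The text change is one sentence and one line, and nobody on schedule is affected. The practical cost falls on delayed participants. With Visit 2 on day 28, a two-day slip triggers a redraw and an eligibility check in a village setting whose laboratory is in Navrongo, about 25 to 45 minutes' drive from the study villages (7.4.1). Anyone who then fails would be randomized but undosed, hence outside the ITT population (11.6.1) and replaced under 11.10.5. Footnote b's present rule already allows this, and under blinding it is unlikely to bias the comparison.

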# TAKeOFF – LEDoxy: Doxycycline to improve filarial lymphedema

|                                                               | Visit 4
2 months
follow-up a | Visit 5
4 months
follow-up b | Visit 6
6 months
follow-up c | Visit 7
8 months
follow-up d | Visit 8
10 months
follow-up e | Visit 9
12 months
follow-up f | Visit 10
14 months
follow-up g | Visit 11
16 months
follow-up h | Visit 12
18 months
follow-up i | Visit 13
20 months
follow-up j | Visit 14
22 months
follow-up k | Visit 15
24 months
follow-up l |
|---------------------------------------------------------------|-----------------------------------------------|-----------------------------------------------|-----------------------------------------------|-----------------------------------------------|------------------------------------------------|------------------------------------------------|-------------------------------------------------|-------------------------------------------------|-------------------------------------------------|-------------------------------------------------|-------------------------------------------------|-------------------------------------------------|
| Informed Consents/ Assents
(clinical trial and biobanking) |                                               |                                               |                                               |                                               |                                                |                                                |                                                 |                                                 |                                                 |                                                 |                                                 |                                                 |
| Demographic data                                              |                                               |                                               |                                               |                                               |                                                |                                                |                                                 |                                                 |                                                 |                                                 |                                                 |                                                 |
| Lymphedema staging                                            |                                               |                                               | √                                             |                                               |                                                | √                                              |                                                 |                                                 |                                                 |                                                 |                                                 | √                                               |
| Clinical photographs                                          |                                               |                                               | √                                             |                                               |                                                | √                                              |                                                 |                                                 |                                                 |                                                 |                                                 | √                                               |
| History of lymphedema                                         |                                               |                                               |                                               |                                               |                                                |                                                |                                                 |                                                 |                                                 |                                                 |                                                 |                                                 |
| History of ADLA                                               |                                               |                                               |                                               |                                               |                                                |                                                |                                                 |                                                 |                                                 |                                                 |                                                 |                                                 |
| Circumference - Tape                                          |                                               |                                               | √                                             |                                               |                                                | √                                              |                                                 |                                                 |                                                 |                                                 |                                                 | √                                               |
| Circumference - Lymphatech®                                   |                                               |                                               | √                                             |                                               |                                                | √                                              |                                                 |                                                 |                                                 |                                                 |                                                 | √                                               |
| Volume of LE - Lymphatech®                                    |                                               |                                               | √                                             |                                               |                                                | √                                              |                                                 |                                                 |                                                 |                                                 |                                                 | √                                               |
| Ultrasound                                                    |                                               |                                               | √                                             |                                               |                                                | √                                              |                                                 |                                                 |                                                 |                                                 |                                                 | √                                               |
| Medical history                                               |                                               |                                               |                                               |                                               |                                                |                                                |                                                 |                                                 |                                                 |                                                 |                                                 |                                                 |
| Concomitant medication                                        | √                                             | √                                             | √                                             | √                                             | √                                              | √                                              | √                                               | √                                               | √                                               | √                                               | √                                               | √                                               |
| History of relevant medications                               |                                               |                                               | √                                             |                                               |                                                | √                                              |                                                 |                                                 |                                                 |                                                 |                                                 | √                                               |
| Vital signs                                                   |                                               |                                               | √                                             |                                               |                                                | √                                              |                                                 |                                                 |                                                 |                                                 |                                                 | √                                               |
| Physical examination                                          |                                               |                                               |                                               |                                               |                                                |                                                |                                                 |                                                 |                                                 |                                                 |                                                 |                                                 |
| QoL                                                           |                                               |                                               |                                               |                                               |                                                | √                                              |                                                 |                                                 |                                                 |                                                 |                                                 | √                                               |
| Hygiene status                                                |                                               | √                                             | √                                             |                                               |                                                | √                                              |                                                 |                                                 | √                                               |                                                 |                                                 | √                                               |
| Lymphedema management
training                             |                                               | √                                             | √                                             |                                               |                                                | √                                              |                                                 |                                                 | √                                               |                                                 |                                                 | √                                               |
| Laboratory assessment (blood)                                 |                                               |                                               | √                                             |                                               |                                                | √                                              |                                                 |                                                 |                                                 |                                                 |                                                 | √                                               |
| Urine sample collected                                        |                                               |                                               | √                                             |                                               |                                                | √                                              |                                                 |                                                 |                                                 |                                                 |                                                 | √                                               |
| Saliva sample collected                                       |                                               |                                               | √                                             |                                               |                                                | √                                              |                                                 |                                                 |                                                 |                                                 |                                                 | √                                               |
| Pregnancy test                                                | √                                             |                                               | √                                             |                                               |                                                | √                                              |                                                 |                                                 |                                                 |                                                 |                                                 | √                                               |
| In-/Exclusion criteria                                        |                                               |                                               |                                               |                                               |                                                |                                                |                                                 |                                                 |                                                 |                                                 |                                                 |                                                 |
| Randomization                                                 |                                               |                                               |                                               |                                               |                                                |                                                |                                                 |                                                 |                                                 |                                                 |                                                 |                                                 |
| Presence for visit                                            | √                                             | √                                             | √                                             | √                                             | √                                              | √                                              | √                                               | √                                               | √                                               | √                                               | √                                               | √                                               |
| Individual treatment                                          |                                               |                                               |                                               |                                               |                                                |                                                |                                                 |                                                 |                                                 |                                                 |                                                 |                                                 |
| ADLA questionnaire                                            | √                                             | √                                             | √                                             | √                                             | √                                              | √                                              | √                                               | √                                               | √                                               | √                                               | √                                               | √                                               |
| AEs                                                           | √                                             | √                                             |                                               |                                               |                                                |                                                |                                                 |                                                 |                                                 |                                                 |                                                 |                                                 |
| End of study record                                           |                                               |                                               |                                               |                                               |                                                |                                                |                                                 |                                                 |                                                 |                                                 |                                                 | √                                               |

a the 2 months follow-up should take place 61 days (± 7 days) after treatment day 1

c the 6 months follow-up should take place 182 days (± 21 days) after treatment day 1

e the 10 months follow-up should take place 303 days (± 14 days) after treatment day 1

g the 14 months follow-up should take place 425 days (± 21 days) after treatment day 1

i the 18 months follow-up should take place 546 days (± 21 days) after treatment day 1

k the 22 months follow-up should take place 667 days (± 21 days) after treatment day 1

b the 4 months follow-up should take place 121 days (± 10 days) after treatment day 1

d the 8 months follow-up should take place 243 days (± 14 days) after treatment day 1

f the 12 months follow-up should take place 364 days (± 21 days) after treatment day 1

h the 16 months follow-up should take place 485 days (± 21 days) after treatment day 1

j the 20 months follow-up should take place 607 days (± 21 days) after treatment day 1

l the 24 months follow-up should take place 728 days (-28; + 42 days) after treatment day 1

